### Statistical methods

#### Competing events

Participants who die, are put on palliative care or are transferred out of the ICU for any reason due to a worsening condition before achieving successful liberation by day 28 or ICU discharge (whichever occurs first) will be considered to have experienced a competing event. The time from FES treatment administration to death, initiation of palliative care or ICU transfer due to worsening condition will be used for analysis. Participants who reach day 28, are discharged from the ICU or withdraw from the study before experiencing successful liberation from mechanical ventilation or a competing event will be considered right-censored at the earliest of day 28, ICU discharge or study withdrawal.

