#### Key secondary outcomes

The key secondary outcomes—CPF and MEP measured when the participant meets the awakening/comprehension criteria but no sooner than 24 hours after the patient has been extubated—outcome will be sequentially compared between treatment groups using the ITT population in a superiority manner, provided that the active group demonstrates superiority over the sham group in the primary outcome. Each comparison will be conducted at a one-sided significance level of 0.05 using an unpaired t-test. The Wilcoxon rank-sum test will be performed as a supportive analysis to account for any potential violations of the normality assumption.

To control the family-wise type I error, the testing procedure will be carried out in a fixed sequence, starting with the primary outcome, followed by CPF and MEP. The testing will stop at the first rejection failure. This fixed sequence testing procedure guarantees that the family-wise error rate is appropriately controlled across both the primary and key secondary outcomes. Missing data for the key secondary endpoints will be imputed. For participants who have experienced competing events, the worst observed value for that parameter during the study will be imputed. For other participants, under the assumption of missing at random, a linear regression model (multiple imputation) will be used to impute the missing values for CPF and MEP. Predictors in the imputation model will include the following baseline factors: region, race, ethnicity, age, gender, BMI, COPD (yes/no), sepsis (yes/no), clinical frailty scale, steroid use (yes/no) and the Sequential Organ Failure Assessment (SOFA) score. Predictors may be removed if convergence issues arise.

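### CPF and MEP of participants who are never extubated and have no competing event are imputed as missing at random from extubated, awake patients, an implausible assumption that favours the arm with more such failures

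*Protocol article*

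**What the plan says.** Under Key secondary outcomes in the protocol article, CPF and MEP are "measured when the participant meets the awakening/comprehension criteria but no sooner than 24 hours after the patient has been extubated". They "will be sequentially compared between treatment groups using the ITT population in a superiority manner", once active has shown superiority on the primary outcome. The ITT population is every randomised participant (Statistical methods, Primary outcome). On the test: "Each comparison will be conducted at a one-sided significance level of 0.05 using an unpaired t-test". Only a supportive role is given to the Wilcoxon rank-sum test.

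Missing values follow two rules:
- The first is a penalty: "For participants who have experienced competing events, the worst observed value for that parameter during the study will be imputed". No other group is given a penalised value.
- The second rule covers everyone else with a missing value and rests on a different assumption: "For other participants, under the assumption of missing at random, a linear regression model (multiple imputation) will be used to impute the missing values". The listed predictors are all baseline characteristics. Neither treatment arm nor ventilation course is among them.

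The Competing events section decides who falls under which rule. It limits competing events to death, palliative care and ICU transfer because of worsening, when these come before liberation. Anyone else who is unliberated on reaching day 28, leaving the ICU or withdrawing is not in that group; the section says that they "will be considered right-censored at the earliest of day 28, ICU discharge or study withdrawal".

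**The concern.** A participant who is still ventilated at day 28, or who leaves the ICU unliberated for a reason other than worsening, is censored rather than counted as a competing event. If never extubated and never tested, that participant is handled by the second rule and is given the strength predicted for extubated, awake, testable patients with similar baseline factors.

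The Introduction says that expiratory muscle strength independently predicts successful liberation, and that an effective cough predicts it too. On that rationale, participants who could not be weaned are expected to be weaker than weaned participants with the same baseline profile. Missing at random given baseline factors is then implausible for this group.

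Two weaning failures can therefore be handled in opposite ways. One who is transferred for worsening gets the study minimum, and one who stays on the ventilator gets a weaned patient's strength. The difference in two confirmatory, gated endpoints then depends partly on how each arm's failures split between the two rules.

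**Working it through.** **The plan's own figures.** By Schoenfeld's formula, events = 4(1.96 + 1.2816)² / (ln 1.7)² = 42.03 / 0.2816 = 149.3, so 150. Participants = 150 / 0.55 = 272.7, against 272 stated. Both reproduce and neither is disputed. If exactly 55% are liberated, 0.45 × 272 = 122 participants are not. The article does not split these into competing events and others, and it gives no power or expected values for CPF or MEP.

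**Notation.** For each arm, C is the share with a competing event, and U is the share never extubated, never tested and without a competing event. Let m be the mean in tested participants (taken as equal in both arms), w the worst observed value, and g = m − w. Assume that imputed values average m.
- Arm mean under the plan: m − g·C.
- Arm mean if U also takes the worst value: m − g·(C + U).
- Active minus sham under the plan: g·(C_sham − C_active).
- Active minus sham under the uniform rule: the plan's difference plus g·(U_sham − U_active).

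The two rules therefore differ by g·(U_sham − U_active). Nothing else in this simplified model affects the gap.

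**Assumed inputs (not in the documents).** Tested mean CPF is 60 L/min and the worst value is 5, so g = 55. Liberation proportions are derived from the stated subdistribution hazard ratio of 1.7 and 55% overall: with 45.5% in sham, active is 1 − (1 − 0.455)^1.7 = 64.4%, and the average is 55%.

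**Results for CPF.**
- *Upper-end case.* Competing events 30% sham v 22% active. U is 1 − 0.455 − 0.30 = 24.5% v 1 − 0.644 − 0.22 = 13.6%. Plan: 55 × 0.08 = 4.4 L/min. Uniform rule: 55 × (0.545 − 0.356) = 10.4. Shift: 55 × 0.109 = 6.0.
- *Competing events 35% v 25%.* U is 19.5% v 10.6%. Plan: 5.5. Uniform rule: 10.4. Shift: 55 × 0.089 = 4.9.
- *Most failures are competing events.* U is 5% v 3%, so C is 49.5% v 32.6%. Plan: 55 × 0.169 = 9.3. Uniform rule: 10.4. Shift: 55 × 0.02 = 1.1.

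The first two cases treat everyone neither liberated nor with a competing event as never tested. That remainder also contains withdrawals, participants reintubated within 7 days who may have been tested from 24 hours, and participants extubated and tested later, since no latest test time is given. For those competing-event rates, 24.5% v 13.6% is therefore an upper bound on U.

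**Check in SD units.** A simulation used 136 per arm, 2,000 runs, 10 imputations without arm in the model, a one-sided 0.05 test and no true effect in measurable participants. With C at 20% in both arms and U at 25% sham v 15% active, the plan gave 0.00 SD and rejected in 4% of runs. The uniform rule gave +0.26 SD and rejected in 41%. With U reversed, the plan again gave 0.00 SD and the uniform rule −0.27 SD. With C and U equal across arms, neither rule produced a difference.

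**The case against.** **Different strategies for death and for continued ventilation are not in themselves an error.** This stands. With equal strength in tested participants, the uniform rule's 10.4 L/min comes only from the difference in liberation, so it is not a true value that the plan misses. Calling 4.4 shrunken presupposes a composite estimand. What remains is that the imputation assumption conflicts with the article's own rationale. It is implausible, though not false by construction.

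**A reader might infer that the rule flatters the arm with more weaning failures of any kind.** The documents do not support that. Death, palliative care and ICU transfer for worsening are penalised with the worst value. Only an excess of failures without a competing event is favoured.

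**A reader might infer a large false-positive risk.** With 40% failures in both arms, split C 15% and U 25% in active against C 25% and U 15% in sham, the simulated plan gave +0.27 SD and rejected in 42% of runs. This is not the error rate of the planned procedure. CPF and MEP are tested only after a primary win, and with 60% liberated in both arms that win would be rare unless liberation were merely earlier in active.

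**The SAP may add detail.** It may include arm in the imputation or sensitivity analyses. The split between the two rules, however, is fixed in the article's text, so this is not something left open.

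**Conclusion.** The point holds in this limited form. Participants without a competing event who are never extubated and never tested are imputed as if their strength were that of extubated, awake patients, and the article's own rationale makes this implausible. The shift equals the gap between tested mean and worst value times the between-arm difference in the share of such participants. With an assumed 55 L/min gap, that is about 1 L/min for 5% v 3% and about 6 L/min for 24.5% v 13.6%, the latter an upper-end case. The documents do not say where in this range the trial lies.

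The likely effect is dilution of the active-sham difference, because testing follows a primary win for active and sham may then hold more of these participants. The direction is not certain: it reverses if stimulation moves participants from death or palliative care to prolonged ventilation. The primary outcome is unaffected.

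**What to change.** Decide this before database lock and unblinding. The Trial status section gives recruitment as complete in January 2026 and analysis from about April 2026.
- Apply the worst-value rule already used for competing events to participants censored unliberated at day 28 or ICU discharge who were never extubated and never tested.
- Keep multiple imputation for participants extubated but untested and for withdrawals.
- Include treatment arm in the imputation model.
- Report the present missing-at-random handling as a sensitivity analysis.

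No new data collection is proposed. The statistical cost is a larger point mass at the worst value in the confirmatory t-test. The Wilcoxon test copes with this better but is only supportive, so its result should be read beside the t-test. The endpoint will also reflect liberation as well as strength, and the report should say so.

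### The imputation model listed for CPF and MEP leaves out randomised arm, so model-imputed values carry no treatment difference and the key secondary estimates shrink toward zero

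*Protocol article*

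**What the plan says.** All of this is in the Protocol article, Statistical methods, Key secondary outcomes.

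- **Comparison.** CPF and then MEP are "sequentially compared between treatment groups using the ITT population in a superiority manner", provided the primary outcome succeeds. "Each comparison will be conducted at a one-sided significance level of 0.05 using an unpaired t-test". Testing is in fixed sequence and ends at the first failure.
- **Participants with a competing event.** "For participants who have experienced competing events, the worst observed value for that parameter during the study will be imputed".
- **Everyone else with a missing value.** "under the assumption of missing at random, a linear regression model (multiple imputation) will be used to impute the missing values for CPF and MEP".
- **Model terms.** "Predictors in the imputation model will include the following baseline factors: region, race, ethnicity, age, gender, BMI", followed by COPD and sepsis, and closing with "clinical frailty scale, steroid use (yes/no) and the Sequential Organ Failure Assessment (SOFA) score". That makes eleven terms, all measured at baseline.
- **Flexibility.** "Predictors may be removed if convergence issues arise". Adding a term is not mentioned.

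Randomised arm appears nowhere in this description, and imputing separately by arm is not mentioned either.

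**The concern.** The completed data are used to compare arms, but the model that completes them does not contain arm. Randomisation balances the eleven baseline terms, so they cannot stand in for it. A missing active value and a missing sham value with the same baseline profile are drawn from the same distribution, which pools both arms. If stimulation really raises CPF or MEP, the participants filled in by the model show none of that gain.

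Missing at random given baseline factors does not repair this. If the treatment works, the outcome depends on arm even after conditioning on those factors, so a model without arm is misspecified for the comparison that follows.

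CPF and MEP are the only secondary outcomes in the alpha-controlled sequence. The reported differences and intervals would be too close to zero. Because CPF is tested first, a failure caused by the imputation would also deny MEP its test.

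The number of values affected may not be small. Both measures need extubation, a wait of at least 24 hours and the awakening criteria (Secondary outcomes). Two groups go to the regression model when unmeasured: participants censored without a competing event (Competing events), and liberated participants who never meet the awakening criteria.

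**Working it through.** **Inputs from the article.** Allocation is 1:1. The targets are 150 liberations and about 272 participants, with at least 55% liberated (Sample size). The test is one-sided at 0.05. No effect size, standard deviation or missing rate is given for CPF or MEP.

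**The plan's own figure.** The Schoenfeld formula with a subdistribution hazard ratio of 1.7, two-sided 5% and 90% power gives 150 events, and 150/0.55 = 272.7. Both reproduce. They concern the primary outcome and are used here only to set 272/2 = 136 per arm.

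**Assumptions.** The true difference is d among participants without a competing event. In each arm a share c gets the worst value and a share m is model-imputed. Values are missing at random within arm.

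**Step 1, equal shares by arm.**
- With arm in the model, observed and imputed values both carry d. The worst values carry nothing. Expected difference = (1-c)d.
- Without arm, only observed values carry d. Expected difference = (1-c-m)d.
- Ratio = (1-c-m)/(1-c).

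At c = 0 and m = 10%, 20%, 30% the ratio is 0.90, 0.80, 0.70. At c = 25% it is 0.65/0.75 = 0.87, 0.55/0.75 = 0.73 and 0.45/0.75 = 0.60.

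**Step 2, unequal missingness (c = 0).** Let a and s be the model-imputed shares in the active and sham arms. Imputed values centre on the pooled observed mean, which lies p·d above the sham mean, with p = (1-a)/(2-a-s). The completed difference is d[(1-a) + (a-s)p] = d·2(1-a)(1-s)/(2-a-s). This factor is the harmonic mean of (1-a) and (1-s), so it is below 1 whenever anything is imputed. For a = 15% and s = 35% it is 2 × 0.85 × 0.65/1.50 = 0.74.

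**Step 3, simulation.** The settings were 272 participants, a true difference of 0.40 SD, covariate R² of 0.20, 20 imputations, Rubin's rules, a one-sided 0.05 test and 1,000 trials per cell. The effect size and R² are assumed.

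| c | m | Estimate without arm (algebra) | Estimate with arm (algebra) | Power without arm | Power with arm |
|---|---|---|---|---|---|
| 0 | 10% | 0.360 (0.36) | 0.395 (0.40) | 0.895 | 0.942 |
| 0 | 20% | 0.325 (0.32) | 0.399 (0.40) | 0.825 | 0.900 |
| 0 | 30% | 0.277 (0.28) | 0.402 (0.40) | 0.657 | 0.885 |
| 25% | 10% | 0.262 (0.26) | 0.296 (0.30) | 0.422 | 0.502 |
| 25% | 20% | 0.224 (0.22) | 0.295 (0.30) | 0.322 | 0.469 |
| 25% | 30% | 0.185 (0.18) | 0.284 (0.30) | 0.218 | 0.433 |

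The estimates without arm follow the algebra closely. At c = 25% the estimates with arm fall slightly below 0.30, so the simulated ratios there (0.262/0.296 = 0.89, 0.224/0.295 = 0.76, 0.185/0.284 = 0.65) sit a little above the algebraic ones.

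**Step 4, no true effect (c = 0).** Without arm, the rejection rate is 0.024 at m = 20% and 0.021 at m = 30%, against a nominal 0.05. With arm it is 0.045 and 0.058.

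**The case against.** **Arm may be implied.** The text says what the model will include, not that it includes nothing else, and arm is not usually called a baseline factor. A model fitted separately in each arm would list just these covariates, and the SAP, which is not at hand, may say so. This is possible, and it is why the conclusion is tied to the model as written. But the article is not silent: it gives an explicit list and foresees only removals. Nothing in it supports the reading that arm is included.

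**The error is conservative and confined.** This stands. Rejection under the null is below nominal, the primary analysis is untouched, and CPF and MEP are tested only if the primary succeeds. But the plan states a superiority comparison under missing at random. It does not present the imputation as a deliberate no-effect assumption.

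Three stronger readings are tempting, and the article does not support them:

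- *All imputed values lose the treatment effect.* Participants who die, move to palliative care or leave the ICU because they are worsening get the worst observed value outside the regression. If such events differ by arm, that part of the contrast is not shrunk, and the ratio in Step 1, which assumes equal c, does not apply directly.
- *Up to 45% of values are affected, since only 55% need be liberated.* The non-liberated include those same competing-event participants. The article does not give the split, so 45% cannot be taken from it as the model-imputed share.
- *The model is also wrong for omitting maximum inspiratory pressure or the other of CPF and MEP.* These are measured under the same post-extubation and awakening conditions, so a participant missing one will usually miss all. Using baseline covariates is not in itself an error.

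**Conclusion.** The point holds for the model as the article describes it. Missing CPF and MEP values of participants without a competing event are drawn with no expected arm difference, which pulls both treatment estimates toward zero and costs power. In the simulated settings at c = 0 and m = 30%, power falls from 0.885 to 0.657.

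The direction needs only a true effect and some model-imputed values. The size rests on m and c, which the article does not state, on equal shares by arm, and, for power, on the assumed 0.40 SD difference and R² of 0.20. The harm is an understated effect and possible false failures in the fixed sequence. A reader should not infer inflated type I error or a threat to the primary result.

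**What to change.** Before unblinding, state in the SAP and in the article either that randomised arm is a predictor in the imputation model, or that imputation is run separately within each arm. If arm is a predictor, exempt it from the rule that lets predictors be removed when the model does not converge. If the SAP already does one of these, correct the article so that the two agree.

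The cost is a sentence of wording and about one line of imputation code, with no new data. The Trial status section puts the end of recruitment in January 2026 and the start of analysis at an estimated April 2026, so the change should be dated and documented before the database is locked.

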### Oversight and monitoring

The sponsor, Liberate Medical LLC, is acting as the coordinating centre for this trial. All authors are the sole members of the study scientific advisory board. As this study is deemed to be non-significant risk, there is no requirement for a formal data monitoring committee. Instead, an independent physician will serve as the study medical monitor and review all reportable events to monitor for incidence of serious events that would warrant modification or termination of the trial. The medical monitor may recommend study modification or termination because of concerns over participant safety or issues. This notification will be submitted in writing to the Sponsor for consideration and final decision. All protocol changes will be communicated by the sponsor to relevant parties.

### Adverse event reporting and harms

The investigator or designee will record all adverse device events, serious adverse events, serious adverse device events and unexplained adverse device events and device deficiencies in the source document as well as in each participant’s eCRF with information about:

Diagnosis and relevant clinical findings.Date of onset.Date of recovery or the current status of adverse event.Severity.Treatment.Relation to investigational product.Relation to the investigational procedure.Action taken with study treatment.Seriousness of the adverse event.

All adverse device events, serious adverse events, serious adverse device events and unexplained adverse device events and device deficiencies will be reported to the sponsor within one business day of being made aware of the event and will be reported to the investigational review board/ethics committee as per applicable regulations.

### Frequency and plans for auditing trial conduct

An independent physician will serve as the study medical monitor and review all reportable events for serious events that warrant modification or termination of the trial. The medical monitor may recommend study modification or termination because of concerns over participant safety or issues. Such a recommendation would be submitted in writing to the Sponsor for consideration and final decision.

Risk-based monitoring activities will be conducted according to the CIP, ISO 14155:2020 GCP, 21 CFR 812.46 and regulatory guidance relevant to this clinical study. Periodic monitoring will be completed on-site and/or by remote visit from representatives of the sponsor or CRO who will check the eCRFs for completeness and accuracy, verify eCRFs with source documents, review site compliance, review administrative records and confirm that all adverse events have been reported as required. In addition, frequent communications by the study monitors will ensure that the investigation is conducted according to the CIP, regulatory requirements and good clinical practice.

Study close-out will be performed by the study monitor upon completion of the study. The close-out visit will consist of reconciliation of all remaining data inconsistencies, obtaining current status determination for all unresolved adverse events and review of administrative records. In addition, the monitor will perform final investigational product reconciliation for all products received, used, shipped or disposed of during the study.

## Discussion

This randomised controlled trial is a pivotal evaluation of the efficacy of abdominal functional electrical stimulation, delivered via the VentFree device, to assist ventilator weaning in critically ill adults. While the design posed a number of challenges, it also offered the opportunity to create innovative solutions to existing problems.

After the cause of respiratory failure has improved and when patients are clinically stable, the current standard of care is to evaluate a patient’s readiness for liberation using a spontaneous breathing trial (SBT), which is typically a period of minimal ventilator support. If the patient does well during the SBT, he/she can be considered for extubation; otherwise, the patient is returned to full mechanical ventilation with the process repeated at a later date.^38^ As such, we have developed a standardised weaning protocol (online supplemental appendix B) that should reduce variability in this study.

The optimum stimulation parameters for abdominal functional electrical stimulation have yet to be established. As such, the treatment protocol has been chosen based on physiological and practical considerations. First, respiratory muscle atrophy has been shown to occur most rapidly within the first week of mechanical ventilation.^7 8^ Therefore, we wish to start the intervention as early as possible within this period. Second, the force evoked from a muscle by electrical stimulation can decline over time because of repetitive activation of the same motor units. Therefore, we reason that limiting the stimulation session duration to 30 min will help to ensure a strong muscle contraction throughout the session. The practical considerations include the availability of research staff on weekends and possible interference with clinical protocols. The exact stimulation frequency, pulse width and amplitudes applied here have been used in a range of other abdominal functional electrical stimulation studies, including our pilot studies.^27 28 30^

As this trial is recruiting participants from up to 30 different ICUs across four different countries, we believe the results will be generalisable globally. Furthermore, we envision that our inclusion and exclusion criteria will enable inclusion of most patients who are at risk of respiratory muscle atrophy due to mechanical ventilation.

